#### Comparators

Our 2-stage randomization crosses two Stage 1 interventions with two Stage 2 interventions, creating a factorial structure **(**Fig. 3**)**.

**Fig. 3 Fig3:**
[figure not shown]
Factorial Structure

*Testing Effect 1* compares the effectiveness of CBT with fluoxetine medication in improving patient-centered outcomes over the 24-week trial. It answers the question that all patients, parents, and clinicians ask when beginning treatment for an anxiety disorder: “Is it better to begin with CBT or medication?”

*Testing Effect 2* compares 2 interventions in their effects on patient centered outcomes by week 24 in patients for whom the Stage 1 intervention fails to induce clinical remission by week 12: (a) optimizing the initial treatment modality alone; and (b) adding the other modality to optimization of the first. It answers the question that arises soon thereafter in the treatment of most patients: “If clinical response to the initial treatment is less than ideal, is it better to continue and optimize that initial treatment, or to add the other treatment modality to the first?”

*The interaction* effect assesses whether one of the 4 treatment sequences – CBT➔optimized CBT; CBT➔optimized CBT + medication; medication➔optimized medication; medication➔ optimized medication+CBT – is significantly better or worse than predicted from the two main effects alone. It should be noted that these interaction effects are not the same interactions that might be addressed in a classical factorial trial design because the treatments and groups are not concurrent, nor are the same conditions present for combining groups [130]. Nevertheless, testing this effect will address another question that arises during clinical treatment: “Which sequence of treatments will produce the best response – fully optimized CBT alone; CBT with the addition of medication; fully optimized medication alone; or optimized medication with the addition of CBT?” It also answers the question of whether the effects of combined treatment are additive or multiplicative relative to the effects of monotherapy.

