## Methods

### Specific aims

In 404 predominantly underserved, ethnic minority children who have a DSM-5 anxiety disorder, we will conduct a 24-week Sequential Multiple Assignment Randomized Trial (SMART) **(**Fig. 2**)** with the following aims:(a) We will assess whether beginning with Cognitive Behavioral Therapy (CBT) or fluoxetine medication is more effective in improving youth-rated anxiety symptoms over the 24-week intervention (“Main Effect 1”)(b) If the initial intervention fails to induce clinical remission by week 12, we will assess whether optimizing the initial treatment modality alone, or adding the other modality while optimizing the first, yields better symptom improvement by week 24 (“Main Effect 2”)(c) We will assess whether one sequence of treatment modalities – i.e., CBT➔CBT; CBT➔CBT + med; med➔med; med➔med + CBT -- is significantly better or worse than predicted from the two main effects.(d) We will assess the stability of treatment response for ≥12 months following completion of the 24-week trial.We will explore the moderating effects of patient characteristics on Main Effects 1 and 2, and on their interaction, to identify tailoring variables that will support personalized interventions for selection of initial and subsequent sequencing of treatment modalities for pediatric anxiety disorders.We will explore the differential treatment effects of our interventions on other patient centered outcomes, including: well-being; life-satisfaction; self-efficacy; family, social, and school functioning; sleep; emotion-regulation; coping with change; comorbid psychiatric symptoms; and adverse treatment effects.

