#### Non-randomized, treatment-as-usual (TAU) group

It is possible that medication and CBT will produce similar therapeutic responses in our patient population. We would like to be able to estimate the effect of each treatment and each treatment sequence in our SMART design against usual treatment in real-world settings. Therefore, we will include a non-randomized TAU group consisting of patients who satisfy all study eligibility criteria, pass the 3-level screen, an decline participation in the randomized trial, but who consent to participate in a truncated study measurement sequence. In addition to the eligibility measures for these patients, we will acquire a small subset of measures (SCARED-41, CAIS, CBCL, treatment expectations, ADIS Supplemental Service Form) at the same time points as in the randomized group – at baseline and weeks 6, 12, 18, and 24, as well as the quarterly follow-up assessments thereafter.

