### Data analysis plans

Upon completion of the final trial participant, we will complete a final database review and finalize data queries, then lock the trial database for final analysis. To evaluate baseline comparability, we will compare demographic and clinical characteristics, and trial outcome measures, at baseline between treatment groups. Continuous baseline measures will be summarized by mean (SD) or median (IQR), and categorical measures by frequency (percent). Standardized group differences will be computed and presented for all baseline variables.

We will conduct an intent-to-treat analysis, by which subjects will be analyzed according to randomized intervention, consistent with standard practice in clinical trials. Distributions of outcome variables will be graphically examined; normalizing transformations will be applied if needed. The 24-week continuous measures of primary and secondary trial outcomes will be compared between treatment groups using general linear models, with the 24-week measure as the dependent variable. SMART design groups will include Stage 1 randomized group and Stage 2 randomized group. The randomization stratification factors (age group,clinical site, and dichotomized baseline parent SCARED-41), as well as baseline measures of the trial outcome (Youth SCARED ratings), will be included as model covariates. Results will be summarized by treatment group means (SDs) and mean treatment group differences (and 95% confidence intervals). No interim analyses are planned.

To **test Main Effect 1**, a 2-group (Stage 1 randomization) analysis of covariance will be used, comparing subjects randomized to medication first to those randomized to CBT first [53, 54, 197]. To **test Main Effect 2** among Stage 1 non-remitters, a 2-group analysis of covariance will also be used, comparing (a) non-remitting subjects randomized at Stage 2 to optimization of their Stage 1 monotherapy, vs (b) non-remitting subjects randomized at Stage 2 to combination treatment (medication+CBT or CBT + medication) across levels of Stage 1 randomization. Finally, to test whether one sequence of treatment modalities (CBT➔CBT; CBT➔med; med➔med; med➔CBT) is significantly better or worse than predicted from the two main effects, an interaction term of Stage 1 randomization with Stage 2 randomization will be added to the model. The addition of the interaction term will allow estimation and testing of each of the 4 treatment sequences [53, 54, 197].

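### The Stage 1 by Stage 2 interaction cannot show whether combined treatment is additive, and it cannot single out one sequence

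*Protocol article*

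**What the plan says.** The Comparators section opens with the statement that "Our 2-stage randomization crosses two Stage 1 interventions with two Stage 2 interventions, creating a factorial structure". The four cells are CBT optimized, CBT optimized with medication added, medication optimized, and medication optimized with CBT added. None is untreated.

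The protocol then gives the interaction three jobs:

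- **Finding a sequence that stands out.** Specific aims, item (c), asks whether one sequence "is significantly better or worse than predicted from the two main effects". The Abstract, Comparators and Data analysis plans repeat this.
- **Addressing a clinical question** that begins "Which sequence of treatments will produce the best response" (Comparators).
- **Judging additivity:** "It also answers the question of whether the effects of combined treatment are additive or multiplicative relative to the effects of monotherapy". This sentence stands only in Comparators.

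Comparators also carries a caveat, that "these interaction effects are not the same interactions that might be addressed in a classical factorial trial design", on the ground that the treatments and groups are not concurrent and the conditions for combining groups differ. It then goes on to the second and third jobs.

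In Data analysis plans the implementation is that "an interaction term of Stage 1 randomization with Stage 2 randomization will be added to the model", followed by "The addition of the interaction term will allow estimation and testing of each of the 4 treatment sequences". The next paragraph adds replication of remitters, inverse-probability weights and robust standard errors for the comparison of the four sequences. Outside this structure, "we will include a non-randomized TAU group".

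**The concern.** The two factors are which treatment came first and whether the other was added. They are not CBT yes/no crossed with medication yes/no. Additivity of two treatments is a statement about the second kind of table, which needs a cell with neither. Without that cell, a significant interaction could be taken as evidence that CBT and fluoxetine do not combine additively when it may only reflect a difference between them as monotherapies. A null result could be taken as additivity when there is strong synergy.

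The protocol's own expectations make the first misreading likely. Hypothesis 1a expects fluoxetine to do better than CBT, and Sample size and power takes from the earlier multimodal trial a combination gain that is larger over CBT alone than over medication alone. Both point to a non-zero interaction whatever the truth about synergy.

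The second issue is that a single product term cannot carry a statement about one sequence out of four.

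**Working it through.** **The plan's own figures.** No effect size or power is stated for the interaction. The figures in Sample size and power (two-sided 0.05, 80% power) reproduce closely:

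- Main Effect 2 at 0.40 SD: 4 × (2.80/0.40)² ≈ 196, against 194 stated.
- Total: 194/(0.6 × 0.8) = 404.2, against 404.
- Main Effect 1 with 324: 2.80 × √(4/324) = 0.311 SD, against 0.31.

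The fault is in the stated inference, not in this arithmetic.

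**Step 1. What the interaction contains.** Work in SD units of benefit. Let b be the untreated level, C and M the effects of CBT and medication alone, and s the departure of the combination from additivity. First assume that the combination gives the same result in either order and in both non-remitter populations:

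- CBT = b + C
- CBT+med = b + C + M + s
- med = b + M
- med+CBT = b + M + C + s

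I = (med+CBT − med) − (CBT+med − CBT) = (C + s) − (M + s) = C − M. The departure s cancels.

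| C | M | s | Combination (b = 0) | I |
|---|---|---|---|---|
| 0.5 | 0.6 | 0 | 1.1 | −0.10 |
| 0.5 | 0.6 | +0.5 | 1.6 | −0.10 |
| 0.5 | 0.6 | −0.3 | 0.8 | −0.10 |
| 0.5 | 0.5 | 0 | 1.0 | 0 |
| 0.5 | 0.5 | +0.4 | 1.4 | 0 |
| 0.5 | 0.5 | −0.3 | 0.7 | 0 |

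These values are illustrative; the protocol gives none.

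**Step 2. Relaxing the assumption.** Without it, I = (CBT − med) + (med+CBT − CBT+med). The second bracket is the difference between the combination cells, by order or by population. If only s depends on order, I = C − M + (s after medication − s after CBT). Any synergy common to both orders still drops out, and what is left is mixed with C − M.

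**Step 3. The other contrasts do not rescue it.** In the Step 1 model Main Effect 2 is (C + M)/2 + s, which does not separate s. Two different truths give the same four cells:

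- b = 0, C = 0.4, M = 0.6, s = 0: cells 0.4, 1.0, 0.6, 1.0
- b = 0.3, C = 0.1, M = 0.3, s = 0.3: cells 0.4, 1.0, 0.6, 1.0

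No analysis of these four cells can tell additivity from synergy of 0.3 SD.

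**Step 4. One degree of freedom.** Fit the two main effects to a balanced 2 × 2 table; the four residuals are ±I/4. Each of these single-cell departures gives I = −0.4 and residuals (−0.1, +0.1, +0.1, −0.1) in the order CBT, CBT+med, med, med+CBT:

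- CBT+med raised by 0.4
- med raised by 0.4
- CBT lowered by 0.4
- med+CBT lowered by 0.4

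The test detects a departure but cannot say which sequence produced it.

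**Step 5. Best sequence.** Take cells 0, a, d and d + a with a and d positive (medication better than CBT, adding better than optimizing). Then I = a − a = 0, yet med+CBT is clearly best. The ranking comes from the four means, not from the interaction.

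**Step 6. Replicated remitters.** In the weighted model the interaction also absorbs remission rates. Assume 40% ± 5 points, from the protocol's 10-point difference, so non-remission is 0.55 after medication and 0.65 after CBT. An equal add-on gain of 0.4 in non-remitters then gives 0.55 × 0.4 − 0.65 × 0.4 = −0.04.

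**The case against.** Several points on the other side are sound.

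- A reader might infer that item (c) of Specific aims also claims to test additivity. It does not, and neither do the Abstract and Data analysis plans. That claim is one sentence in Comparators.
- A reader might infer that the trial cannot say which sequence is best. The documents do not support that. With both main effects and the product term the model is saturated over the four sequences, so all four means are estimable, and the comparison of sequences is specified with replication, weights and robust standard errors. Only the attribution of that question to the interaction test is wrong.
- Exact reduction to C − M needs a combination effect that does not vary by order or population. This trial exists partly to study order, and CBT non-remitters and fluoxetine non-remitters are different groups. Step 2 allows for this: the interaction then holds more terms, but still does not isolate s.
- Describing an interaction as a departure from the main effects is ordinary shorthand. The fault is the reference to one sequence.
- No analysis, sample size or decision rule rests on the additivity sentence, and the protocol does not say how a significant or null interaction would be reported. The misreadings are a risk, not a stated plan.

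The caveat in Comparators does not cure the additivity claim. It rests on non-concurrence, does not mention the missing untreated cell, and is followed by the claim. The usual-treatment group does not help either: it is non-randomized, not untreated, and not in the interaction model.

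**Conclusion.** The point holds in two limited parts.

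First, the additivity sentence in Comparators is wrong for this design. The departure from additivity is not identified from four actively treated cells: the interaction can be non-zero under pure additivity (−0.10 SD with 0.5 and 0.6 SD monotherapies) and zero under strong synergy (equal monotherapies, s = +0.4). The exact values assume an order- and population-invariant combination. The lack of identification does not.

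Second, a one-degree-of-freedom interaction cannot show that one sequence in particular is better or worse than predicted. In balanced cells all four depart by I/4. Nor does it by itself show which sequence is best, although the planned sequence means can.

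This is a fault in what the protocol says it will conclude. Randomization, sample size and the planned models stand. It should be corrected because it concerns a named aim.

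**What to change.** 1. In Comparators, delete the sentence on additive or multiplicative effects.
2. In the Abstract, Specific aims item (c), Comparators and Data analysis plans, describe the interaction as a test of whether the gain from adding the other modality differs by Stage 1 treatment. Say whether that gain is meant among non-remitters or across whole sequences, since Step 6 shows that the two differ.
3. In Comparators, state that the best-sequence question is answered by contrasts of the four sequence means, with confidence intervals, from the weighted and replicated model already in Data analysis plans.
4. State how multiplicity is handled for those contrasts. The Multiplicity section tests Youth SCARED at 0.05 and applies false-discovery control to secondary, exploratory and subgroup analyses; it does not clearly place sequence contrasts on the primary outcome under either rule.

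The cost is some rewording and one added sentence on multiplicity. No new data, participants or change to randomization are needed. What is given up is a conclusion about additivity that the design cannot support.

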#### Study population and setting

Los Angeles County (LAC) is one of the most racially, ethnically, and socioeconomically diverse regions in the world [131]. Our study population will be recruited from our vast LAC clinical network serving predominantly underserved, impoverished, and ethnic minorities. Locating these recruitment and treatment sites in LAC provides great efficiency in study infrastructure while simultaneously yielding a remarkable diversity of settings including primary pediatrics care (CHLA Care Network, AltaMed sites), a private health care plan (Kaiser site), a free-standing children’s hospital (CHLA site), and community mental health clinics serving primarily youth with Medi-Cal insurance, the federal Medicaid program in California (Hathaway-Sycamore, UCEDD, LAC+USC, Children’s Bureau of Southern California sites) or commercial insurance (LifeStance Health California site). The total number of patients seen in our age range across these 9 sites is > 300,761 annually (601,522 over 2 years of recruitment), and 2.9% of them already carry a diagnosis of anxiety disorder in their electronic medical record. We would need to recruit only 0.49% of all patients already diagnosed with an anxiety disorder across these sites to meet our target total of 404. We expect several times more than this number of patients to be identified through systematic screening efforts at each site, further enhancing the feasibility of recruiting our target number.

*All clinical care components of the study, including CBT and medication management, will be paid through the standard mechanisms at each clinic.* At all participating sites, with the exception of Kaiser, LifeStance Health, and CHLA’s care network facilities, Medi-Cal pays for services without patient co-pays. Even these exceptional facilities have ~ 20% of their patients with Medi-Cal. Those with private insurance have small co-pays that families can usually afford.

### Study participants

We will aim for a sample that represents best practice in high quality clinical care by including most comorbidities. We will not exclude based on past diagnoses or treatment, in part because current diagnosis and treatment will be the focus of this study, and in part because it will not be possible to ascertain the validity of past diagnoses or quality of past treatments reported by patients or parents. Not excluding on these past variables will also enhance the generalizability of this study’s findings.

#### Inclusion criteria

Patient at one of our clinical study sitesAge 8–17 inclusive (this age range allows the same CBT intervention and outcome measures for all participants),SCARED-5 screening score ≥ 3 (see “Screening” below) and score ≥ 25 on the SCARED-41,A diagnosed anxiety disorder (generalized anxiety, separation anxiety, social anxiety, panic disorder) on the clinician-administered Schedule for Affective Disorders and Schizophrenia for School-Aged Children, Computerized version (K-SADS-COMP)CAIS (Child Anxiety Impact Scale) > 8 (representing at least moderately severe illness).We will include patients and at least one parent/caregiver who are fluent in either English or Spanish to ensure accurate assessment, as most standardized measures are normed only in those languages, and sites have limited capacity to provide translation services in other languages. Trial staff and clinicians will be fluent in both languages, and all selected outcome measures will have been previously validated in both languages. Based on comprehensive survey data, we estimate that only 0.3% of families at our sites will not have one parent/caregiver who speaks either English or Spanish.

#### Exclusion criteria

Patients currently receiving psychotherapy. Prior psychotherapy of any kind, including CBT, is not exclusionary.Patients currently receiving an SSRI, SNRI, or benzodiazepine. Prior use of any of these medications is not exclusionary.Patients with a severe neurological disorder or unstable medical condition, as determined by medical chart and medical history review by the site director and Principal InvestigatorFemales who are pregnant or sexually active but not using an effective method of birth control (potential adverse fetal effects of medication [132])Patients who have taken Monoamine Oxidase Inhibitors (MAOIs), pimozide, thioridazine, olanzapine, tricyclic antidepressants (TCAs), antipsychotics such as haloperidol and clozapine, anticonvulsants such as phenytoin and carbamazepine within 2 weeks prior to starting the study, as these can interfere with metabolism of fluoxetineColumbia-Suicide Severity Rating Scale [104, 133] score of:
3 AND “access to crisis level support is unavailable”, OR4 if “frequency, duration, and deterrent” all = 1 AND treatment in a specialty mental health clinic is not available, OR4 if “frequency, duration, or deterrents” are > 1, OR5To map onto the cognitive and socio-emotional demands of the CBT protocol, we will exclude youths who are likely to be functioning at a developmental level outside the minimum age for the treatment manual (age 8): namely, youths who are placed outside of a general education classroom for > 50% of the school day or require a one-on-one classroom aide to maintain placement in a general education class, or are performing academically below the 3rd grade level in reading and language arts.Current, clinically significant Obsessive-Compulsive Disorder (OCD) or Post-Traumatic Stress Disorder (PTSD). Coping Cat CBT was not designed for, nor is it an appropriate treatment for, OCD or PTSD. The most appropriate evidence-based treatments for these two disorders are Exposure and Response Prevention for OCD, and Trauma-Focused CBT for PTSD. Those two treatments differ markedly from the Coping Cat procedures clinicians will be taught in our study. It would be clinically inappropriate and arguably unethical to train clinicians in Coping Cat and then assign study patients to them who have disorders that cannot be effectively treated with Coping Cat. Moreover, clinically significant PTSD usually requires combined medication and Trauma-Focused CBT from the outset, making these youth inappropriate for this clinical trial in which participants are initially assigned to a monotherapy.
OCD will be diagnosed using the clinician-administered KSADS-COMP.PTSD will be assessed using the Lang Child Trauma Screen [134, 135]. To optimize the representativeness of our sample, we desire a very low false positive rate for a screener – i.e., we want a screener cutoff with high specificity for diagnosing PTSD. ROC curves for this screener [134, 135] indicate that by requiring a score of ≥10 on the parent report for child reaction to past trauma, we will miss diagnosing approximately 22% of true PTSD cases but we will not exclude any who are incorrectly diagnosed. Therefore, we will exclude youth for whom (a) either the parent OR the child reports a history of trauma on this screener, AND (b) the parent reaction score is ≥10Youth currently in foster care. We have extensively explored with the CHLA IRB and our clinical sites the procedures required to enroll these youth in research treatment studies. This includes permission of the court (both the patient’s court-appointed attorney and the judge who oversees the case), the Department of Children & Family Services, and biological parents (depending on the status of the case and who has medical rights), a process that requires institutional lawyers and that can take many months, requiring an extraordinary amount of time and effort on the part of the study team. Potential treatment issues that include the need to obtain additional court approvals when randomized to the medication arm will also likely create a delay in care and systematically affect the medication arms of our trial. Finally, participation requires the de facto permission of the foster parents to ensure the youth will attend clinical appointments. Although we would like to include youth in foster care, it simply is not feasible.

